## Abstract

**Background:**

Interdental spaces are particularly susceptible to biofilm accumulation and gingival inflammation, which contribute to periodontal diseases and their systemic associations. While interdental brushes (IDBs) are recognized as the most effective method of interdental cleaning, their efficacy depends on proper adaptation to the interdental space. Calibration with a colorimetric probe may enhance their effectiveness and comfort. However, evidence directly comparing calibrated and noncalibrated IDBs, especially in young adults, a key target group for preventive strategies, remains limited. The Hygiene of Interdental Junctions in Adults (HIJA) trial was designed to address this gap.

**Objective:**

This protocol aims to compare the clinical, microbiological, and acceptability outcomes associated with calibrated versus noncalibrated IDBs in young adults, focusing on interdental inflammation, periodontal indices, and microbiota composition.

**Methods:**

The HIJA trial is a monocentric, randomized, controlled, single-blind, and parallel-arm study. Overall, 50 healthy, nonsmoking adults aged 18‐30 years will be randomized (1:1) to receive either calibrated or noncalibrated IDBs. Participants will perform daily interdental cleaning in addition to conventional toothbrushing for 3 months. The primary outcome will be the reduction in interdental inflammation, expressed as the change in bleeding on probing at 3 months. Secondary outcomes will assess differences in interdental microbiota composition (16S ribosomal RNA sequencing), periodontal indices (plaque index, gingival index, probing depth, and clinical attachment loss), and user acceptability measured through the Theoretical Framework of Acceptability questionnaire at 1, 2, and 3 months.

**Results:**

The HIJA trial will generate evidence on whether calibrated IDBs provide additional benefits over noncalibrated brushes in reducing interdental inflammation and improving oral health in young adults.

**Conclusions:**

HIJA findings could contribute to the implementation of clinical guidelines and preventive strategies for interdental hygiene in daily practice.

## Introduction

Oral health is a cornerstone of general well-being and systemic health [1-3]. Among the multiple ecological niches of the oral cavity, interdental spaces represent unique sites with minimal host defense mechanisms. Their anatomical configuration predisposes them to bacterial colonization and biofilm accumulation, which in turn promotes local inflammation and increases the risk of periodontal disease [4,5]. Periodontal diseases are strongly associated with systemic conditions, including cardiovascular disease, diabetes, adverse pregnancy outcomes, and certain cancers, making early prevention a public health priority [1-3].

The interdental microbiota plays a pivotal role in this process. A balanced microbiota contributes to oral homeostasis, while dysbiosis triggers gingival inflammation and subsequent periodontal destruction. Interdental cleaning, therefore, represents a key strategy to prevent dysbiosis [6,7]. Conventional toothbrushing cannot access interdental areas, which highlights the need for complementary interdental hygiene practices [8].

Current evidence indicates that interdental brushes (IDBs) are the most effective and widely recommended method of interdental cleaning, outperforming dental floss and wooden sticks in reducing gingival inflammation and plaque accumulation. Several meta-analyses and network analyses have confirmed their superiority, while observational studies have shown their acceptability in daily use [4,9]. However, substantial heterogeneity exists among IDBs, particularly regarding size, shape, and calibration. Calibration with a colorimetric probe ensures optimal adaptation of IDB to interdental space, thereby improving mechanical efficacy and user comfort [10].

Despite these insights, there is a paucity of clinical evidence comparing calibrated versus noncalibrated IDBs in young adults, a critical population in which preventive strategies should be implemented before the onset of irreversible periodontal damage [11]. To date, few randomized controlled trials have demonstrated that daily calibrated IDB use significantly reduces interdental inflammation and dysbiosis in young adults [6,7]. No study has yet addressed whether such calibration provides a measurable advantage in real-life daily practice compared to noncalibrated IDBs.

The Hygiene of Interdental Junctions in Adults (HIJA) trial is designed to address the following research question, formulated according to the Population, Intervention, Comparison, and Outcome framework: In healthy young adults aged 18‐30 years (Population, P), does the daily use of calibrated IDBs (Intervention, I) lead to a greater reduction in interdental inflammation compared with the daily use of noncalibrated IDBs (Comparator, C), measured as bleeding on probing (BoP) at 3 months (Outcome, O)?

## Methods

### Trial Design

This clinical study named HIJA is designed as a monocentric, randomized, controlled, 2 parallel-arm, and single-blind clinical study (ratio 1:1; Figure 1). The protocol is presented in accordance with SPIRIT (Standard Protocol Items: Recommendations for Interventional Trials) guidelines [12].

**Figure 1. F1:**
[figure not shown]
Flowchart diagram of Hygiene of Interdental Junctions in Adults study. IDB: interdental brush.

### Study Setting

The HIJA study will be conducted within the Odontology Department of the Hospices Civils of Lyon, France.

### Study Population

#### Eligibility Criteria

##### Inclusion Criteria

Eligibility criteria will be (1) participants between 18 and 30 years of age, (2) who have given their free, informed, and express written consent, (3) affiliated with a French social security scheme, and (4) living or working in Lyon or the Lyon metropolitan area.

Periodontal health will be required for inclusion, in accordance with the 2017 World Workshop classification [13], defined as the absence of gingival inflammation or active attachment loss. A reduced but stable periodontium, such as mild localized recession without probing depth ≥4 mm or generalized involvement, will be considered consistent with periodontal health and may include cases corresponding to Stage I periodontitis when such findings are localized, noninflammatory, and clinically stable.

##### Exclusion Criteria

Exclusion criteria will be (1) individuals with a tobacco addiction, (2) currently participating in another study related to oral hygiene, (3) at high risk of infective endocarditis, (4) with chronic medical conditions such as type 1 or 2 diabetes, (5) who have taken antibiotic treatment during the month preceding the start of the study, (6) pregnant or breastfeeding women, (7) deprived of their liberty by a judicial or administrative decision, (8) receiving psychiatric care, (9) admitted to a health or social care facility for purposes other than research, (10) subject to a legal protection measure (guardianship and curatorship), (11) not affiliated with a social security scheme or beneficiaries of a similar scheme, (12) with fewer than 20 natural teeth, (13) currently performing interdental hygiene and/or daily mouthwashes, (14) wearing orthodontic appliances, (15) with periodontal disease (stage II or higher according to the 2017 Chicago classification [ie, probing pocket depth, PPD ≥4 mm and/or clinical attachment loss, CAL ≥4 mm] and/or generalized, >30% of sites), active caries, or undergoing dental treatment, and (16) under judicial protection.

### Materials Description

#### Colorimetric Probe

The IAP CURAPROX calibrating probe is a graduated conical instrument with a rounded tip (Figure 2A and B). The working part comprises colored bands from the point to the base corresponding to IDBs by increasing diameter. The largest section of each colored band corresponds to the cleaning efficiency diameter of the relevant brush. The nonworking part has a click-fastening joint for the attachment of a handle for easier use and access to the interproximal spaces at the back of the mouth.

**Figure 2. F2:**
[figure not shown]
Procedure for using the colorimetric probe to determine the appropriate interdental brush size. (**A**) Colorimetric probe, (**B**) color indication (yellow) corresponding to the measured interdental space, (**C**) available interdental brushes color-coded by size, and (**D**) use of the selected interdental brush in the interdental space.

Interdental diameters were coded as 1=blue, 2=red, 3=pink, 4=yellow, and 5=green. The procedure consists of introducing the IAP CURAPROX probe into the vestibular interdental space, inserting it fully, then noting the color emerging from the interdental space on the vestibular side. This corresponds to the color code of the IDB most suitable for the interdental space in question. The pressure used to place the probe tip at the base of the interdental sites was approximately 50 N/cm^2^ (0.20 gram force).

#### Interdental Brushes

The IDBs used in this study are from the CPS range of CURAPROX (Curaden; Figure 2C and 2D). These IDBs consist of cylindrical nylon fiber brushes mounted on a CURAL wire core coated with synthetic material to prevent galvanic or traumatic effects. The brushes are supplied with ergonomic plastic handles to facilitate grip and insertion in posterior sites. Each CPS pack comprises five IDBs with the following characteristics: (1) a specific color code corresponding to the brush size (Table 1); (2) an access diameter, defined by the gauge of the CURAL wire core, which determines the minimal interdental space into which the brush can be inserted; and (3) an effective cleaning diameter, defined by the length and elasticity of the synthetic bristles covering the working part of the device.

**Table 1. T1:** Characteristics of interdental brushes used in the Hygiene of Interdental Junctions in Adults study.

Color code	Access diameter (mm)	Cleaning diameter (mm)
Blue	0.6	2.2
Red	0.7	2.5
Pink	0.8	3.2
Yellow	0.9	4
Green	1.1	5

### Interventions

In the intervention group, participants will receive IDBs with diameters individually determined by the dentist using a colorimetric probe to ensure optimal adaptation to each interdental space. In the control group, participants will receive IDBs prescribed by the dentist without calibration by a probe. In both groups, the dentist will visually assess the morphology of the interdental spaces, including the presence or partial loss of interdental papilla, to ensure that the prescribed brushes can be safely and comfortably inserted. This clinical evaluation will complement the calibration procedure in the intervention group and will guide professional judgment in the control group. All participants will be instructed to use IDBs once daily, in addition to their regular toothbrushing routine, for a duration of 3 months. They will not be allowed to use complementary techniques (dental floss, mouthwashes, etc) during the period of the study. All participants will be naive users of IDBs at baseline, as individuals already performing interdental hygiene will be excluded according to the study criteria.

Individual instructions on interdental brushing hygiene techniques will be provided by the dentist, who will first ensure that each participant is able to handle the IDBs correctly and safely, demonstrating sufficient manual dexterity and cognitive ability to perform the technique as instructed. Each participant will be provided with a logbook at the baseline visit to record daily IDB use by ticking the corresponding day for adherence monitoring. The logbook will be reviewed at every visit to assess compliance.

### Procedures and Follow-Up Schedule

Participants will attend 4 visits: baseline (T0), week 1 (T1), month 1 (T2), and month 3 (T3).

#### Clinical Assessments (At All Visits)

The oral examination in accordance with clinical practices will be carried out by a dentist who will report the following clinical parameters:

BoP: dichotomous gingival index (GI) reporting the presence or absence of BoP after 30 seconds (0=absence of bleeding after 30 s and 1=presence of bleeding after 30 s). A total of 4 sites are recorded per tooth (mesiobuccal, distobuccal, mesiopalatine, and distopalatine) [14,15].Gingivitis score (GI): measured by visual observation from 0 to 3 (0=no inflammation; 1=slight change, slight inflammation in color, and little change in texture; 2=moderate, moderate inflammation, redness, edema, and hypertrophy, tendency to bleed on probing; 3=severe, marked redness, inflammation, hypertrophy, and tendency to spontaneous bleeding). Gingivitis score=sum of GI scores divided by the number of total sites [16].Dental plaque score (Rustogi Modified Navy Plaque Index): according to the Navy Plaque Index modified by Rustogi et al [17], the presence of plaque deposits is sought on the vestibular and lingual surfaces of the teeth. Each tooth face is divided into 9 areas to which a dichotomous score is assigned (0=absence of plaque and 1=presence of plaque). Thus, for each tooth, 18 measurements are carried out. This index makes it possible to detect minimal differences at the partial level of the marginal or interproximal zones, or at the total level of the oral cavity [17].PPD score: a measure indicating the distance separating the top of the marginal gingiva from the bottom of the periodontal pocket. The measurement is expressed in millimeters. Overall, 4 sites are recorded per tooth (mesiobuccal, distobuccal, mesiopalatine, and distopalatine) [18].CAL score: addition of PPD and recession height, which is the distance separating the enamel-cementum junction from the bottom of the pocket. In total, 4 sites are recorded per tooth (mesiobuccal, distobuccal, mesiopalatine, and distopalatine) [15].Interdental bleeding: bleeding was assessed dichotomously following interdental brushing (0=absence of bleeding after insertion and removal of the brush and 1=presence of bleeding after insertion and removal). All interdental sites were recorded at each visit.

PPD and CAL will be assessed following the criteria defined by the consensus report of the 2017 World Workshop on the Classification of Periodontal and Peri-Implant Diseases and Conditions [13], using the US Williams PDT sensor probe (Zila-Pro-Dentec Inc) at a pressure of 20 g. Based on severity-defined stages of interdental CAL and tooth loss, complexity, extent, and distribution, they included a full oral examination of 6 sites on each permanent tooth. All measures will be performed on all teeth except for third molars. One calibrated dentist trained will perform the periodontal evaluations of all participants. Intraclass correlation coefficients for PPD and CAL will be determined at the level of the site. The intraexaminer coefficients for CAL will be, respectively, from 0.80 and 0.85, and from 0.75 and 0.85 for probing depth.

#### Interdental Microbiota Sampling (T0 and T3)

Interdental plaque will be collected from 4 sites (15-16, 25-26, 35-36, and 45-46). Each IDB used for sampling will be stored in RNase- and DNase-free tubes at –20°C within 4 hours and transferred later to the GenEPI platform (Hospices Civils of Lyon, Lyon, France) for long-term storage at −80°C. Analysis will be performed by 16S ribosomal RNA gene sequencing to determine microbiota composition in a single batch. Briefly, a 16S ribosomal RNA gene fragment comprising V3 and V4 hypervariable regions will be amplified using an optimized and standardized 16S amplicon library preparation. Sequencing will then be performed using a 250-base pair paired-end sequencing protocol on an Illumina MiSeq platform (Illumina). Bioinformatic analysis will then be performed using the QIIME2 software (Caporaso Lab, Northern Arizona University) in its latest version.

#### Questionnaires

Participants will complete 2 questionnaires: (1) First, the baseline oral hygiene questionnaire at T0 (Multimedia Appendix 1) that analyzes habits, frequency, and duration of daily hygiene; and (2) second, the Theoretical Framework of Acceptability (TFA) administered at T1, T2, and T3 (Multimedia Appendix 2). The TFA includes dimensions of perceived effort, intervention coherence, affective response, perceived effectiveness, and self-efficacy, allowing assessment of feasibility and long-term integration. The trial participation schedule is detailed in Table 2.

**Table 2. T2:** Trial participation schedule.

Procedures and visits	Timeline			
	T0 (baseline)	T1 (1 week / T0)	T2 (1 month / T0)	T3 (+3 months / T0)
Prescreening	✓			
Eligibility screening	✓			
Informed consent	✓			
Questionnaires	✓	✓	✓	✓
Oral hygiene attitudes and practices**^a^**	✓			
Acceptability of IDB^b^^c^		✓	✓	✓
Oral examination	✓	✓	✓	✓
BoP^d^	✓	✓	✓	✓
Interdental bleeding	✓	✓	✓	✓
GI^e^	✓	✓	✓	✓
Plaque index	✓	✓	✓	✓
PPD^f^	✓	✓	✓	✓
CAL^g^	✓	✓	✓	✓
Interdental microbiota sampling	✓			✓

a Multimedia Appendix 1 lists oral hygiene attitudes and practices.

b IDB: interdental brush.

c Multimedia Appendix 2 lists the acceptability of interdental brush.

d BoP: bleeding on probing.

e GI: gingival index.

f PPD: probing pocket depth.

g CAL: clinical attachment loss.

### Outcomes

#### Primary Outcome Measures

Reduction in interdental inflammation, expressed as the proportion of sites with BoP at 3 months (T3), comparing calibrated versus noncalibrated IDBs.

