### Sample Size

The reduction in gingival bleeding was considered the primary outcome variable, and an estimate of the mean difference in reduction was used to calculate the sample size. Based on a 2-sided α of .05, 80% power, an intraclass correlation of 0.8, and an expected 25% difference in BoP between groups, a total of 50 participants (200 sites) are required. Taking into account a dropout rate of 10%, in order to have 50 participants at the end, 56 participants (28 per group) will be included.

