#### Data Analysis

Statistical analyses will be conducted on both the intention-to-treat and per-protocol populations. All randomized participants will be included in the intention-to-treat analysis, while the per-protocol analysis will exclude those with major protocol deviations, such as nonuse of IDBs. Missing data will be addressed using multiple imputation by chained equations with Monte Carlo Markov Chain methods, assuming data are missing at random. Descriptive statistics, including means, SDs, medians, interquartile ranges, and frequencies, will be calculated. Between-group comparisons will be performed using Student 2-tailed *t* test or the Wilcoxon test for continuous variables and the Chi-square test for categorical variables. Changes over time will be assessed using mixed linear models, with log-transformed bleeding values when appropriate. Fixed effects will include independent variables such as age, socioeconomic status, and experimental group, while subjects will be included as a random effect to account for repeated clinical bleeding measurements. Estimated coefficients for each independent variable will be tested against the null hypothesis of zero, with significance set at *P*<.05. Analyses will be performed using SPSS (IBM Corp), SUDAAN (RTI International), and R software (R Development Core Team). Exploratory analyses will also be performed to assess potential correlations between CAL and participants’ adaptation and compliance with IDB use, as evaluated through the TFA questionnaire and the compliance logbook.

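### The primary BoP outcome is stated both as a change and as a 3-month level, and no single primary analysis is named that would settle which

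*Protocol article*

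**What the plan says.** The protocol article describes the primary outcome in four places:

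- **Abstract, Methods:** "expressed as the change in bleeding on probing at 3 months". This is a change.
- **Introduction, research question:** it asks about a greater reduction, but the outcome is "measured as bleeding on probing (BoP) at 3 months (Outcome, O". This mixes change and level.
- **Primary Outcome Measures:** a reduction, "expressed as the proportion of sites with BoP at 3 months (T3), comparing calibrated versus noncalibrated IDBs". The quantity described is a level at T3.
- **Sample Size:** "an estimate of the mean difference in reduction was used to calculate the sample size", which is a change. The effect is then given as "an expected 25% difference in BoP between groups", without saying whether it is absolute or relative, or a level or a change.

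Secondary Outcome Measures also lists the evolution of BoP at T1, T2 and T3.

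Data Analysis compares groups by Student's t test "or the Wilcoxon test for continuous variables and the Chi-square test for categorical variables". Changes over time go into mixed linear models with a subject random effect. The fixed effects named there, as examples, are age, socioeconomic status and group. Bleeding values may be log-transformed. Both intention-to-treat and per-protocol populations are analyzed. The section does not say which of these is the primary analysis, or whether the t or Wilcoxon test is applied to T3 values or to changes.

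BoP is measured at T0 and at every later visit. Allocation is 1:1 without stratification.

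**The concern.** A level at T3 and a change from T0 are different variables with different variances. They also respond differently to chance imbalance at baseline. If the plan supports both and does not name one analysis, the primary result can be chosen after the data are seen. With about 25 per arm and no stratification, a baseline difference large enough to matter is quite possible.

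The conflict also reaches the sample size. If the Outcomes section is right, the trial was sized on a different variable from the one it will test. If the Abstract is right, the change in BoP at T3 appears as both a primary and a secondary outcome.

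**Working it through.** **The plan's own figure.** The dropout step reproduces: 50 / (1 − 0.10) = 55.6, rounded up to 56, or 28 per arm. The 50 itself can be neither confirmed nor refuted, because no SD and no control-arm BoP are given. Read as a comparison of means at two-sided 0.05 and 80% power, 25 per arm implies a standardized difference of

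d = √[2(1.960 + 0.842)² / 25] = 0.79.

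For a 25-point difference that is an SD of 25 / 0.792 = 31.5 points. This does not show whether the SD belongs to T3 levels or to changes. The stated intraclass correlation of 0.8 cannot stand in for r: 200 sites / 50 participants = 4 sites each, so it may be a between-site correlation.

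**Why the two analyses can disagree.** In complete data, (T3 difference) − (change difference) = (baseline difference), exactly. Assume equal SDs at T0 and T3 and write D for the chance baseline difference in SD units. With no treatment effect, the expected T3 difference is rD and the expected change difference is (r − 1)D. For r between 0 and 1 these have opposite signs. With 25 per arm the standard error of D is √(2/25) = 0.283. An imbalance of one standard error gives:

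- r = 0.3: level +0.085 SD, change −0.198 SD
- r = 0.5: level +0.141 SD, change −0.141 SD
- r = 0.8: level +0.226 SD, change −0.057 SD

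The gap is 0.283 SD each time, or 0.283 / 0.792 = 36% of the difference that 25 per arm can detect with 80% power.

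**Precision.** With equal SDs, variance relative to the T3-level test is 1 (level), 2(1 − r) (change) and 1 − r² (ANCOVA on baseline). Power = Φ(2.802/√V − 1.960), where V is the relative variance and 2.802 = 0.792 × √(25/2), which sets the level test at 80%. Because r is not in the documents, a range is shown.

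| r (assumed) | V: level / change / ANCOVA | Power: level / change / ANCOVA | ANCOVA n per arm for 80% |
|---|---|---|---|
| 0 | 1 / 2.00 / 1.00 | 80 / 51 / 80% | 25 |
| 0.3 | 1 / 1.40 / 0.91 | 80 / 66 / 84% | 23 |
| 0.5 | 1 / 1.00 / 0.75 | 80 / 80 / 90% | 19 |
| 0.8 | 1 / 0.40 / 0.36 | 80 / 99 / 99.7% | 9 |

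Simulation (10,000 runs per r) agreed: 80/51/79% at r = 0, 81/65/83% at 0.3, 80/80/89% at 0.5 and 80/99/99.6% at 0.8. At r = 0, ANCOVA lost about one point, from the estimated slope and its degree of freedom.

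If the change test is instead the one with 80% power, level / ANCOVA power is 91/93% at r = 0.3, 80/90% at 0.5 and 42/84% at 0.8.

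**Effect of unequal SDs.** If the baseline SD is k times the T3 SD, the change variance becomes 1 + k² − 2rk. At k = 0.5 and r = 0.3 that is 1 + 0.25 − 0.30 = 0.95, against 0.91 for ANCOVA. The poor showing of the change score at low r therefore depends on k being near 1.

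**Why baseline adjustment settles the choice.** If T3 = a + τ·arm + b·T0, then T3 − T0 = a + τ·arm + (b − 1)·T0. The arm effect τ is the same in both. In simulation the two fits agreed to below 2×10⁻¹⁵. The identity holds for absolute change. It does not hold for percent change, or when only the outcome is log-transformed.

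**The case against.** The strongest reply is that this is loose drafting of one intended outcome. The research question, the Outcomes section, the Abstract and the Sample Size section all speak of a reduction or a change, and two of them then describe it by the T3 measurement. That may be what was meant, but the text as it stands still yields two different variables, and Data Analysis does not choose between them.

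A reader might infer that the trial ignores baseline BoP. The documents do not support that. The fixed effects are given as examples, so the list is open. A mixed model with T0 as one of the repeated outcomes would use baseline, and a t test on change uses it by subtraction. The full covariate list may also stand in a document not shown. The firm finding is the conflict in the definition and the unnamed primary analysis.

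A reader might also infer that ANCOVA is worth a third more participants (1/0.75 = 1.33). That holds only at r = 0.5, and r is not stated. Entry requires the absence of gingival inflammation, so baseline BoP may lie in a narrow range near zero and r may be low. At r = 0.3 the gain over a T3-only test is about 4 points of power, and at r = 0 there is none.

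Finally, unadjusted tests on level or change are both valid under randomization. The shifts shown above are conditional on a chance imbalance and are not a bias of the design. That objection stands.

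**Conclusion.** The concern holds as an inconsistency in the current text. The primary outcome is a change in two places, a T3 level in one and a mixture in another, and no single primary analysis is named. The level and change estimates differ by the chance baseline difference. One standard error of that difference is 0.28 SD with 25 per arm, assuming equal SDs at T0 and T3. The powers of the two tests coincide only at r = 0.5 under that same assumption.

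Baseline adjustment is a recommendation that follows from this, not a correction of an error. In large samples it is never less precise than either alternative. Here its gain over a T3-only test ranges from nothing (or a loss of about one point) at r = 0 to about 20 points at r = 0.8. If r is low and the SDs are similar at the two visits, the gain over a change score is large; if the baseline SD is much smaller, that gain shrinks. The size of the benefit cannot be fixed from the documents. Nor do they show that the sample size of 50 is wrong, only that it is not clear which variable it refers to.

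**What to change.** 1. Align the Abstract, the research question, Primary Outcome Measures and Sample Size on one variable: each participant's percentage of sites with BoP at T3, on a stated scale. In Sample Size, say whether the 25% is absolute or relative and that it refers to this variable.
2. In Data Analysis, name one primary analysis: a regression of T3 BoP on arm with baseline BoP as covariate, in all randomized participants. Label the mixed model and the unadjusted t or Wilcoxon test as secondary or sensitivity analyses, and say which variable the unadjusted test uses.
3. If bleeding is to be log-transformed or expressed as a percent reduction, fix that in advance, because level and change then no longer give the same arm effect automatically.

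The cost is a few sentences in five places. Baseline BoP is already collected, so no visit, measurement or participant is added. The change should be made before unblinding.
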